**Methods/design:**

To determine the effectiveness of our web-BI, we apply a two-arm randomized controlled trial (RCT) study design, with baseline assessment at study entry and a three month follow-up assessment. Adolescents aged 16 to 18 years from Belgium, the Czech Republic, Germany, and Sweden will be randomly assigned to either the fully electronically delivered brief intervention group (*N* = 400) or an assessment only control group (*N* = 400) depending on their screening for risky substance use (using the CRAFFT). Recruitment, informed consent, randomization, intervention and follow-up will be implemented online. Primary outcomes are reductions in frequency and quantity of use of alcohol and drugs other than alcohol over a 30 day period, as well as consumption per typical occasion. Secondary outcomes concern changes in substance use related cognitions including the constructs of the Theory of Planned Behaviour, implementation intentions, and stages of change. Moreover the study addresses a number of moderator variables, including age of first use, general psychopathology and quality of parent–child relationship.

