### Assessment

Those eligible and willing to participate in the study will receive comprehensive baseline assessment questionnaires containing socio-demographic characteristics, such as age, gender, educational/vocational information, as well as their weight which will be the base for an individualised and personalised feedback in the later intervention (weight is necessary to calculate Blood-alcohol-concentration). Items concerning current substance consumption (primary outcomes) and cognitive items concerning substance use (secondary outcomes) will be assessed at baseline and follow-up. A number of potential moderator variables are included in the baseline assessment to allow for subgroup analyses. All measures are based on established scales or self-constructed according to the literature (see *Instruments* section). All assessment material will be pilot-tested for appropriateness and duration as completing the survey should not take long in order to avoid attrition.^c^

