#### Description of the intervention

The overarching goal of the intervention is to encourage reduced alcohol consumption and abstinence from any illicit drugs.^d^ The single-session intervention is fully automatised and electronically delivered yet interactive. It works with presenting tailored feedback to the participants’ responses in the earlier assessment (i.e., consumption levels) and provides choice options on how to react to this feedback. This interactivity simulates a face-to face “dialogue”, which aims for an empathic style, avoids argumentation, rolls with resistance and aims at creating a dissonance between actual and desired behaviour and raising self-efficacy. To achieve these goals, our intervention basically consists of three components. First, participants will receive personalised feedback on their substance consumption patterns including the associated risks (related to health and other consequences) and comparisons to a normative reference group. Second, participants engage in interactive MI-based exercises that have been proven effective in prompting readiness to change by encouraging the participant to consider the costs and benefits of their current substance use and actual change. Finally, the intervention will include practical advice concerning alternative behaviour in tempting situations, with a focus on peer resistance skills to raise self-efficacy beliefs and implementation intentions. All components will be described in more detail below. The whole intervention can be completed in approximately 10 to 15 minutes.

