#### Secondary measures

In addition to the behavioural outcome variables described above we assess a number of potential and theoretically plausible moderator and mediator variables, as well as several cognitive-level outcomes. Specifically, we assess the following moderators: *Age of first use*, *General Psychopathology*, using a short version of the Symptom Checklist (SCL-K 9) [79] and *Child Disclosure*[80], as an indicator of parent–child relationship quality. Positive parent–child relationship is a protective factor for adolescent substance use [81] and has been consistently shown to be related to lower likelihood of adolescent substance use [82] and variables related to adolescent substance use, such as self-control, competence, and peer affiliations [83]. Regarding potential mediators and cognitive outcomes we rely on socio-cognitive constructs based on major psychological models predicting health behaviour change, such as Ajzen’s Theory of Planned Behaviour (TPB) [84], and Prochaska & Di Clemente’s Transtheoretical Model (TTM) [85,86]. Both theories are widely used in clinical practice and health psychology and generalise across many different problem behaviours [87,88]. Specifically, we address *attitudes*, *subjective norms*, *perceived behavioural control*, and *behavioural intentions* as the proximal cognitive antecedents of goal-directed behaviour. Additionally we include a measure of *Implementation Intentions*[89] to address the action planning phase in goal attainment. Implementation intentions are defined as plans that specify the conditions under which target behaviours will be performed and help to ensure that the decision is acted upon [90]. Moreover, we include an algorithm for allocating participants into different *stages of change* concerning their substance use [91-93] hypothesising that progression (such as from precontemplation to contemplation) will be more pronounced in the intervention group compared to the control group. All items are adapted from previous related research.

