### Statistical analyses

To test the efficacy of WISEteens we address the primary research question whether participation in the intervention leads to a decrease in drinking and / or drug consumption other than alcohol at follow-up after three months compared to those adolescents in the assessment-only control group. The main analysis will follow separate analyses for alcohol and drugs. For alcohol consumption we will run multivariate analyses of covariance (MANCOVA) with intervention condition as the independent variable (intervention vs. control group) on the primary dependent variables frequency and quantity (i.e., number of drinks per typical drinking occasion) of alcohol consumption, frequency of binge drinking (AUDIT-C), reductions in weekly drinking and peak drinking. Baseline alcohol units of these variables and change scores (baseline-follow-up) of motivational (i.e., implementation intentions) and the socio-cognitive constructs (i.e., intentions, attitudes, subjective norms, PBC) based on Ajzen’s Theory of Planned Behaviour (TPB) [84] will be included as covariates. For drug use other than alcohol we will analogously run separate analyses of variance (MANCOVAs) on the primary dependent variables frequency and quantity of drug use (DUDIT-C). In addition, we will test whether socio-demographic variables (age, sex, social class), country of residence (Sweden, Germany, Belgium, Czech Republic), general psychopathology, parent–child relationship, age of first use, and stage of motivation to change moderate the outcomes. Moreover we will explore possible mediated effects of our intervention on the various behavioural measures relying on multiple mediation analysis using the syntax of Preacher and Hayes [96] for SPSS, and test direct and indirect effects in a path model using AMOS 18 [97]. Path Analysis is a multivariate technique specifying relationships between observed variables akin to running several regression equations with the advantage that it allows simultaneous testing of several propositions regarding how constructs are theoretically linked and the directionality of significant relationships within one single model [98].

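### The main alcohol MANCOVA adjusts for post-randomisation change in the protocol's own potential mediators, so its condition term does not estimate the total effect of allocation

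*Protocol article*

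**What the plan says.** All references are to the protocol article.

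- **Primary question** (Statistical analyses): "whether participation in the intervention leads to a decrease in drinking and / or drug consumption other than alcohol at follow-up after three months", compared with assessment-only control.
- **Main model** (same section): "The main analysis will follow separate analyses for alcohol and drugs". For alcohol this is a MANCOVA with condition as the independent variable and five drinking variables as dependents.
- **Covariates** (same section): "Baseline alcohol units of these variables and change scores (baseline-follow-up) of motivational (i.e., implementation intentions) and the socio-cognitive constructs". The text names the socio-cognitive constructs as intentions, attitudes, subjective norms and perceived behavioural control.
- **Drug use** (same section): "For drug use other than alcohol we will analogously run separate analyses of variance (MANCOVAs"; no covariates are listed for it.
- **Role of the constructs** (Abstract, Methods/design): "Secondary outcomes concern changes in substance use related cognitions including the constructs of the Theory of Planned Behaviour"; implementation intentions and stages of change are in the same list. Under Secondary measures: "Regarding potential mediators and cognitive outcomes we rely on socio-cognitive constructs based on major psychological models predicting health behaviour change".
- **Target of the intervention** (Description of the intervention): the practical-advice component works "with a focus on peer resistance skills to raise self-efficacy beliefs and implementation intentions".
- **Timing** (Assessment): "cognitive items concerning substance use (secondary outcomes) will be assessed at baseline and follow-up". The Randomisation section places allocation after the baseline questionnaires.

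The mediation and path analyses come later in Statistical analyses, as additional work. No main model without the change scores is described.

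**The concern.** Randomisation protects a comparison of arms that is unadjusted or adjusted for variables fixed before allocation. A change score from baseline to follow-up is not such a variable: half of it is measured three months after allocation. Here the protocol expects allocation to move these variables, and expects that movement to change drinking. Holding them constant asks a different question: how much do the arms differ in drinking among adolescents whose cognitions changed by the same amount?

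Two things are at stake. First, any benefit that acts through intentions, attitudes, norms, perceived control or implementation intentions is credited to the covariates and not to the intervention. A null condition term could not be read as no effect of the intervention. Second, cognitions and drinking are recorded at the same follow-up. Drinking less may itself have changed attitudes or intentions, and unmeasured factors may drive both. Conditioning on the change scores then opens associations that randomisation had closed, so a positive condition term could not be read as the effect of allocation either.

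**Working it through.** **Step 1. Roles and timing.** For the change scores to be legitimate adjusters, allocation must not affect them. The protocol's own text points the other way:

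| Property | Where stated |
|---|---|
| Measured at baseline and again at follow-up | Assessment |
| Allocation precedes the follow-up value | Randomisation |
| Changes in them are secondary outcomes | Abstract, Methods/design |
| Socio-cognitive constructs are potential mediators | Secondary measures |
| Implementation intentions are a target of the intervention | Description of the intervention |
| Change scores are covariates in the main model | Statistical analyses |

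**Step 2. What the condition term estimates.** In a linear model, total effect = direct effect + indirect effect through the constructs. With the constructs in the model and no shared causes or reverse causation, the condition coefficient is the direct effect only. If a share m of a total d = 0.20 is mediated, its expectation is 0.20 × (1 − m). It equals the total only at m = 0 and is zero at m = 1.

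**Step 3. The plan's own power figure.** Sample size section: d = 0.2, one-sided α = 0.05, power 0.80, 50% loss, 400 recruited per arm. This leaves 200 completers per arm. By the normal approximation to the one-sided t test,

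power = Φ(d/s × √(n/2) − 1.645).

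With d = 0.20, s = 1, n = 200: Φ(0.20 × 10 − 1.645) = Φ(0.355) = 64%. The stated 80% is not reproduced at 200 per arm: it needs 310 analysed per arm. That is a separate matter. Here 64% is only the unadjusted reference; with no loss (400 per arm) the reference is 88%.

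**Step 4. Illustration by size of shift.** The documents give neither the shift in the constructs nor their link with drinking. Assumptions: five constructs, inter-correlation 0.4, equal coefficients β, jointly explaining R² = 10–30% of outcome variance, each shifted by δ SD.

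- β = √(R²/(5 + 20 × 0.4)) = √(R²/13), i.e. 0.088 at R² = 0.1 and 0.152 at R² = 0.3
- indirect effect = 5 × δ × β
- adjusted effect = 0.20 − indirect effect
- residual SD = √(1 − R²), i.e. 0.949 and 0.837

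| Shift δ | Indirect (R² 0.1 to 0.3) | Adjusted effect | Power, 200 per arm |
|---|---|---|---|
| 0.2 SD | 0.088 to 0.152 | 0.11 to 0.05 | 32% to 14% |
| 0.1 SD | 0.044 to 0.076 | 0.16 to 0.12 | 50% to 44% |
| 0.05 SD | 0.022 to 0.038 | 0.18 to 0.16 | 59% to 61% |
| 0 | 0 | 0.20 | 68% to 77% |

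Example, δ = 0.2 and R² = 0.1: (0.1123/0.949) × 10 − 1.645 = −0.46, and Φ(−0.46) = 32%.

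**Step 5. Illustration by mediated share.** A simulation used one mediator, total d = 0.20, a mediator-to-outcome slope of 0.3 or 0.5, a one-sided 0.05 test and 4,000 runs per cell.

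| Share m | Mean adjusted estimate | Power, 200 per arm | Power, 400 per arm |
|---|---|---|---|
| 0 | 0.20 | 66–73% | 91–95% |
| 25% | 0.15 | 47–54% | 71–79% |
| 50% | 0.10 | 28–31% | 42–49% |
| 75% | 0.05 | 13–15% | 18–20% |
| 100% | 0.00 | 5% | 5% |

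The model without the mediator gave 0.20 throughout, with about 64% and 88% power. Under full mediation the rejection rate of the adjusted test is α.

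**The case against.** **An unseen analysis plan, or the condensed article format, might resolve it.** This does not help. The article does not leave the covariates open; it names them, in the model that it calls the main analysis.

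**This is really the mediation analysis.** The path model could return direct and indirect effects, but it is presented as exploratory and in addition to the MANCOVA, not as the primary test.

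**Adjustment gains precision.** If the constructs do not move with allocation and there is no reverse causation or shared cause, adjustment does no harm and raises power (68–77% against 64% in the illustration). That stands as arithmetic, but it requires the intervention not to work through the route that the protocol proposes.

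**Stronger readings that the documents do not support:**

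- A reader might infer that the model removes the whole intervention effect. That holds only under full mediation; the protocol calls the mediators potential and gives no mediated share.
- A reader might infer that the estimate is always pulled towards zero. That needs mediation in the same direction as the total effect and no shared causes. With cognitions and drinking measured together, the bias can go either way.
- A reader might take 32–14% as the expected power. It belongs to one assumed shift of 0.2 SD per construct, as large as the whole assumed effect on drinking.
- A reader might infer that the drug models contain the same stated error. Their covariates are not listed, so this is an inference from the word analogously.

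The power figures also describe a univariate one-sided test. The plan's MANCOVA covers five alcohol variables and its omnibus test is not one-sided. The figures ignore the gain from baseline outcome adjustment. They show the mechanism and do not forecast the trial's power.

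**Conclusion.** The concern holds for the alcohol analysis as written. The main model conditions on post-randomisation change in variables that the protocol treats as secondary outcomes and potential mediators, so the condition term is a residual direct effect and does not answer the primary question. This follows from the text and needs no numerical assumption.

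The size cannot be fixed from the documents. It runs from no bias, when allocation leaves the constructs unmoved and there is no reverse causation or shared cause, to complete loss of the effect under full mediation. The intermediate values rest on the assumed shift, inter-correlation and explained variance set out above. For the drug analysis the conclusion is conditional on its using the same covariates.

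This should be corrected before the data are analysed, because neither a null nor a positive condition term from this model could be read as the effect of the intervention.

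**What to change.** Delete all change scores of implementation intentions, intentions, attitudes, subjective norms and perceived behavioural control from the primary alcohol MANCOVA. Keep the baseline values of the outcomes, as already planned. Baseline values of the cognitive constructs may be added if wanted, since they precede allocation. Use change in cognitions only in the secondary-outcome analyses and in the mediation and path analyses that the protocol already describes. State the covariates of the drug MANCOVAs explicitly and, if they were meant to include the change scores, remove them there too.

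The cost is a change of analysis wording. All the baseline values are already collected and no new data are needed. Adding further covariates such as country, sex or age is a matter of preference and is not needed to cure this defect.

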## Abstract

**Background:**

Mid to late adolescence is characterised by a vulnerability to problematic substance use since the consumption of alcohol and illicit drugs is frequently initiated and increased in this life period. While the detrimental long- and short-term effects of problematic consumption patterns in adolescence pose a major public health concern, current prevention programs targeting alcohol- and other substance-using adolescents are scarce. The study described in this protocol will test the effectiveness of a web-based brief intervention aimed at reducing problematic alcohol use and promoting abstinence from illegal drugs in adolescents with risky substance use aged 16 to 18 years old in four EU-countries.

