## Background

Mid to late adolescence constitutes a phase of major developmental changes and age-specific demands associated with the biographic transition into a more adult role [1-3]. While the hallmarks of adolescence are exploration of identity and future prospects [4,5], this phase in the lifespan is also characterized by a certain vulnerability to substance consumption [6] since the consumption of alcohol and illicit drugs is frequently initiated and increased in this life period [7,8].

The European School Survey Project on Alcohol and Other Drugs (ESPAD) periodically reports prevalence rates among students in 35 European countries. Overall, this report demonstrates a considerably high proportion of substance using adolescents particularly concerning early and heavy drinking. In 2007, an average of 90% of the 15–16 year old students in Europe had consumed alcohol at some point in their life. Most of them started to drink alcohol at the age of 13 years [9]. An average of 50% of European students experienced alcohol-intoxication at least once in their lifetime and 39% did so during the last month. Moreover, one of three European students had smoked cigarettes during the past 30 days and one of five had used cannabis at least once in his or her life, which was also true for 7% of the students regarding illicit drugs other than cannabis. Apparently substance use is rarely restricted to the consumption of a single substance as illicit drug consumption is most typically accompanied by alcohol [9]. Such poly-drug patterns appear prevalent among youth in modern Europe as emphasized in the 2009 Annual report by the European Monitoring Centre for Drugs and Drug Addiction [10].

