### Study flow

The landing page will provide five language flags (languages of the four participating countries plus an English Version) for choosing a different language than the language pre-defined by browser options. Those first visiting the page will be asked for registration which requires a user name, e-mail address and a pass word. After registration respondents will be presented with a developmentally appropriate screening tool for adolescents to examine if they fulfil the inclusion criterion of a substance problem. For screening we rely on an adapted version of the CRAFFT^a ^[56] for use of alcohol and drugs. This tool uses six items and has proven criterion validity and appropriateness for identifying substance-related problems among adolescents [57] compared to other screening tools [58]. A CRAFFT score higher than 1 (i.e., at least two questions are answered with yes) demonstrates sensitivity to identify substance problems [58] and is deemed sufficient to be eligible for participating in the study. Besides a positive screen for substance-related problems, participants must be between 16 and 18 years of age. Participants matching the inclusion criteria will then receive study information including confidentiality advice,^b^ the indication of voluntariness of participation, and of human subject protections [28]. They are then asked to electronically give informed consent. Approval for the design and data collection was already obtained from the responsible authorities in each participating country, which are the Ethical Committee of the Chamber of Physicians Hamburg (Germany), Prague Psychiatric Centre (Czech Republic), University Hospital of Antwerp and the University of Antwerp (Belgium), and the Regional Ethics Board in Stockholm (Sweden).

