### Instruments

#### Primary outcomes

The primary outcomes of the study refer to reductions of substance use. As prevalence rates of alcohol are particularly high among youth we distinguish measures for alcohol, which will be the main focus, from those in the broader category of drugs other than alcohol. Specifically we use the Alcohol Use Disorder Identification Test Consumption subscale (AUDIT-C) [75]) for frequency of alcohol consumption, frequency of having five drinks (four for girls) at one occasion (binge drinking), with response options ranging from 1 (*never*) to 5 (*four or more times a week*). Rather than using the third original AUDIT-C item, which measures number of standard drinks consumed per typical drinking occasion (1 = *one or two* to 5 = *ten or more*), and in order to ensure standardised responses across the four participating countries, we use a graphical overview of various types of drinks with the indication to select the number of each drink per typical drinking occasion. This way we can better account for national differences in typical standard drinks while keeping the content of the item. Standard drinks are defined as 10 g ethanol and items are assessed over the past 30 days.

For drugs other than alcohol we analogously use the first three items of the Drug Use Disorder Identification Test (DUDIT) [76] assessing frequency of consumption of drugs other than alcohol, frequency of different types of drugs other than alcohol used at the same occasion (1 = *never* to 5 = *four or more times a week*), and quantity of consumption of drugs other than alcohol on a typical consumption day (1 = *zero* to 5 = *seven or more*).

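### The drug goal is abstinence, but the planned drug analysis compares mean use scores, which cannot separate abstinence from reduction or cessation from initiation

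*Protocol article*

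**What the plan says.** **Goal.** The abstract gives the purpose for drugs as "promoting abstinence from illegal drugs in adolescents with risky substance use aged 16 to 18 years old". Description of the intervention is as direct: "The overarching goal of the intervention is to encourage reduced alcohol consumption and abstinence from any illicit drugs". The end of the Background, the Discussion and the Conclusions state the drug goal in the same way.

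**Outcome and analysis.** The abstract's methods and the Primary outcomes section speak of reductions in use. Statistical analyses asks whether the intervention "leads to a decrease in drinking and / or drug consumption other than alcohol at follow-up after three months". For drugs the plan is then: "we will analogously run separate analyses of variance (MANCOVAs) on the primary dependent variables frequency and quantity of drug use (DUDIT-C". The alcohol analysis that this one mirrors takes baseline values as covariates. Primary outcomes describes three DUDIT items, each scored 1 to 5. The lowest answer is never for the two frequency items and zero for the quantity item. Neither section names abstinence as an endpoint, and the article names no set of participants for the drug analysis.

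**Entry.** Study flow uses one adapted CRAFFT for alcohol and drugs together. The threshold is "A CRAFFT score higher than 1 (i.e., at least two questions are answered with yes". Drug use is not required.

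**Power.** Sample size gives one calculation: d = 0.2, 80% power, one-sided α = 0.05, up to 50% loss to follow-up, and 800 randomised (400 per arm). It is not tied to any outcome.

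**The concern.** The alcohol goal is reduction and the drug goal is abstinence, but the drug analysis copies the alcohol method. This raises three difficulties.

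1. A difference in mean score on a 1 to 5 item does not show whether anyone stopped.
2. Drinkers who take no drugs may enter. On the drug items they start at the lowest category, so they can only stay there or begin using. Participants who stop and participants who start then feed into the same mean.
3. A reader who finds a single 80% power figure will apply it to drugs, although drug users may be only part of the sample.

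The trial could therefore report a drug result that says nothing on its abstinence goal. A null result could be taken as failure when the comparison had little chance of detecting success.

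**Working it through.** **1. What a mean can show.** Take users who all score 3 at baseline.

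- 20% move to 2: mean = 0.2 × 2 + 0.8 × 3 = 2.8, with 0% abstinent.
- 10% move to 1: mean = 0.1 × 1 + 0.9 × 3 = 2.8, with 10% abstinent.

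The means are equal but abstinence differs. Mixing works the same way: one user who stops (3 to 1, change −2) is cancelled by two non-users who start (1 to 2, change +1 each).

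**2. The plan's own sample size.** With d = 0.2, one-sided α = 0.05 and 80% power:

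n per arm = 2 (1.645 + 0.842)² / 0.2² ≈ 310, so 620 completers. With 50% loss, 620 / 0.5 = 1,240 to randomise.

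The stated 800 is not reproduced. The nearest match is a two-sided test with no allowance for loss (393 per arm, 786 in total), which contradicts the stated one-sided test and the stated loss.

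With 800 randomised and 50% loss, 200 per arm remain: power = Φ(0.2 × √(200/2) − 1.645) = Φ(0.355) = 64%. This holds for any outcome at d = 0.2, alcohol included.

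**3. Power for the drug items.** The share of drug users, q, is not in the article, so it is assumed. Suppose non-users sit at the floor with no effect, and users have an effect of 0.2 of their own SD. Let r be the users' mean height above the floor divided by their SD. Then

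d over all = 0.2 √q / √(1 + (1 − q) r²).

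r = 0 is the best case: adjustment for baseline removes all variance between users and non-users. It equals an analysis of users only, with 200q per arm. The calculation treats one item at a time.

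| Assumed share of users | d (r = 0) | Power, 200 per arm, r = 0 | Power, 200 per arm, r = 1 | Power, 400 per arm (no loss), r = 0 |
|---|---|---|---|---|
| 100% | 0.200 | 64% | 64% | 88% |
| 50% | 0.141 | 41% | 31% | 64% |
| 30% | 0.110 | 29% | 21% | 46% |
| 20% | 0.089 | 23% | 16% | 35% |

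Worked line for q = 50%: 0.2 × √0.5 = 0.141; Φ(0.141 × 10 − 1.645) = Φ(−0.231) = 41%.

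With 200 completers per arm, 80% power needs an effect in users of 0.25 SD at q = 100%, 0.35 at 50%, 0.45 at 30% and 0.56 at 20%.

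**4. Power for abstinence among baseline users.** Assume 20% abstinent in one arm and 30% in the other (neither figure is in the article). One-sided, 80% power needs 231 users per arm. With 200 completers per arm, power is about 75% if all are users, 50% at q = 50%, 35% at 30% and 27% at 20%. An abstinence endpoint answers the right question but does not repair the power.

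**The case against.** The strongest reply is that the trial's primary question is about a decrease. Abstinence describes what the intervention promotes, while the outcomes are worded as reductions, and a comparison of frequency and quantity scores answers that question. This stands. A reader might infer that the drug primary is invalid or should be replaced; the article does not support that. Abstinence can also be derived from data already collected, so the gap is in the planned analysis, not in the measurement.

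It is also fair that the share of users is unknown. A reader might infer from the Background that most participants take no drugs, since there "one of five had used cannabis at least once in his or her life", with 7% for other illicit drugs. Those are lifetime figures for students aged 15 to 16 in general. The trial enrols CRAFFT-positive adolescents aged 16 to 18, and Aim and Discussion call the target group poly-drug using. No entry rule enforces that description, but the survey figures do not fix the share either.

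Baseline non-users are not inert: the Background says that use often begins at this age, so the intervention could prevent initiation. The power figures above leave that benefit out. A reader might also quote lower power by ignoring baseline adjustment: with r = 2 it would be 20%, 14% and 11% at shares of 50%, 30% and 20%. The drug analysis is to run in the same way as the alcohol analysis, which adjusts for baseline, so those figures do not describe the planned test.

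Finally, a condensed article may leave the drug analysis set to a fuller document, so its silence does not prove that a whole-sample analysis was chosen. The mismatch between goal and endpoint does not depend on that.

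**Conclusion.** The point holds in a limited form. The article states abstinence as the drug goal in several sections, names no abstinence endpoint, and fixes a drug analysis that cannot distinguish abstinence from reduction. Because drinkers who use no drugs are eligible, that analysis also merges cessation with initiation unless it is restricted to users.

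The power statement should not be carried over to drugs. On assumed shares of 20% to 50% users, an effect of 0.2 SD in users (in the SD left after adjustment) and no effect in non-users, power with 200 completers per arm is at most about 23% to 41%. This is conditional on a share that the article does not give.

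A reader might infer that the whole gap from 80% comes from non-users, or that 80% is right for alcohol. Neither follows. Power is 64% even if every participant uses drugs, because the 50% loss was not carried into the sample size. That is a separate error and it affects alcohol equally.

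**What to change.** - Keep the frequency and quantity analysis for the question about a decrease.
- Add a named drug endpoint: past-30-day abstinence at three months (DUDIT frequency item answered never) among participants who report drug use at baseline. Analyse it by logistic regression adjusted for baseline frequency. Baseline use is recorded before randomisation, so the subset is a fair one to compare.
- Report initiation among baseline non-users separately.
- Do not present the single d = 0.2, 80% power figure as applying to the drug outcome. State the expected share of users and the precision that follows. Do not replace the statement with one that limits the 80% to alcohol, since with the expected loss that would also be wrong.

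No new data are needed. The cost is one more drug analysis, in a smaller set, whose precision is low and will be seen to be low.
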